#### Secondary objectives

The secondary study parameters will be:Changes in stool frequency between groups and over time.Changes in stool consistency in the number of cases in a certain score of the mBSFS, as percentages.

#### Tertiary objectives

Painful defecation.Meeting the Rome IV criteria at baseline, week 9 and week 13.Quality of life of the child, measured by the TAPQOL [34].GI symptoms, such as flatulence and bloating.Gut microbiome:◦ Total faecal microbiota composition, as measured by 16S ribosomal RNA (rRNA) gene sequencing◦ Faecal abundance of specific genera/species as measured by quantitative PCR analysis.◦ Faecal pH and faecal concentration of fermentation products such as short-chain and branched-chain fatty acids.◦ Correlations between stool characteristics and gut microbiota composition, faecal pH or fermentation products.Use of rescue medication.Faecal incontinence (only for completely potty-trained children).The amount of GOS, FOS or placebo supplement consumed, as an indication of compliance, measured in both diaries as well as weighing the tins after the trial.Anthropometrics: weight, height and head circumference measured at baseline and the close-out visit after week 13.Anthropometrics: weight, height and head circumference measured at baseline and the close-out visit after week 13.Dietary intake, as measured by a food frequency questionnaire.

### Participant timeline

After randomisation, patients will enter a 1-week run-in period, after which they will either receive GOS, FOS or a placebo for 8 weeks. Lastly, a 4-week run-out period is in place to investigate whether a possible effect lasts or not. The flow of the study protocol is presented in Fig. 1.

### Sample size

A sample size calculation was performed for stool consistency on a scale from 1 to 5. We used the sample size formula *n* = 2 × (Zα + Zβ)2 × (SD/D)2 per group. Using a probability *α* = 0.05 and a power (1-*ß*) of 80%, the formula simplifies to *n* = 2 × 7.9 × (SD/D)2 per group.

The effect sizes of GOS and FOS versus placebo were estimated based on a study by Closa-Monasterolo et al. who investigated the effect of a mix of chicory inulin with FOS on stool consistency in functionally constipated children aged 2–5 years [26]. Based on these data, an effect size of 0.35 was chosen, with an SD of 0.65. This results in a group size of 54.5. The total number of children to be recruited is 198, that is, 66 per arm assuming a drop-out rate of 20%.

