## Methods

This study (named ‘Inside study’) is a double-blind, randomised, placebo-controlled, multi-centre trial. We aim to enrol 198 children, aged between 1 and 5 years, with FC according to the Rome IV criteria (Table 1).

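### A 20% drop-out from 66 children per arm leaves 52.8, fewer than the 54.5 that the sample size calculation requires

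*Protocol article*

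**What the plan says.** The Sample size section of the protocol article sizes the trial on stool consistency, comparing two group means. The formula is given as "We used the sample size formula *n* = 2 × (Zα + Zβ)2 × (SD/D)2 per group", with the constant fixed by "Using a probability *α* = 0.05 and a power (1-*ß*) of 80%, the formula simplifies to *n* = 2 × 7.9 × (SD/D)2 per group". The inputs are "an effect size of 0.35 was chosen, with an SD of 0.65".

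The result is stated as "This results in a group size of 54.5". The next sentence sets recruitment: "The total number of children to be recruited is 198, that is, 66 per arm assuming a drop-out rate of 20" per cent. The opening of the Methods section repeats the target: "We aim to enrol 198 children".

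The step from 54.5 to 66 is not printed, and nothing in the article gives the drop-out rate any meaning other than the usual one, the fraction of recruited children who are lost.

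**The concern.** A drop-out allowance has one job: after the expected losses, the number the power calculation asked for should remain. To achieve this, the required number is divided by the expected retained fraction. Multiplying it by one plus the drop-out rate gives too few, because the loss applies to the larger recruited number.

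The recruitment figure here looks like the product of that multiplication. If so, 198 children, 20% drop-out and 80% power cannot all hold for the stated difference and SD. This paragraph is the justification for the number of children enrolled, and readers will take it at face value. The allowance may also be tested in practice. The Participant timeline places randomisation before the one-week run-in, so early losses come out of the 66. The Discussion accepts that stopping current medication may lead to unsatisfactory changes in bowel habits.

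**Working it through.** **Inputs**, all from the Sample size section: D = 0.35, SD = 0.65, α = 0.05, power 80%, constant 7.9, drop-out 20%, 66 per arm, 198 in total. The test is taken as two-sided because (1.960 + 0.842)² = 7.85, which matches the printed 7.9; a one-sided test would give about 6.2.

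**1. Reproduce the group size.** 2 × 7.9 × (0.65/0.35)² = 54.49, which agrees with 54.5. With the unrounded quantiles the result is 54.14.

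**2. Reproduce the recruitment figure.**

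| Inflation | From 54.5 | Per arm | Total |
|---|---|---|---|
| n × 1.2 | 65.4 | 66 | 198 |
| n / 0.8 | 68.1 | 69 | 207 |

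Rounding 54.5 up to 55 first changes neither line: 55 × 1.2 = 66.0 and 55 / 0.8 = 68.75, so 66 and 69 again. Starting from 54.14, division gives 54.14 / 0.8 = 67.7, so 68 per arm and 204 in total. Only the multiplication returns the plan's 66 and 198.

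**3. Apply the stated drop-out to the stated recruitment.** 66 × 0.8 = 52.8 per arm. This is 1.7 below 54.5, and it is also below 54.14.

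**4. Drop-out that 66 per arm can absorb.** 1 − 54.5/66 = 17.4%. If 55 completers are wanted, 1 − 55/66 = 16.7%. On the unrounded 54.14, 1 − 54.14/66 = 18.0%.

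**5. Power**, as Φ(D/SD × √(n/2) − 1.96):

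- n = 52.8: Φ(0.5385 × √26.4 − 1.96) = Φ(0.807) = 79.0%
- n = 54.5: Φ(0.5385 × √27.25 − 1.96) = Φ(0.851) = 80.3%

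By the noncentral t distribution the same two sizes give 78.3% and 79.5%. By either method, the drop-out shortfall costs a little over one percentage point.

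**The case against.** The case on the other side is mainly about size, and most of it stands.

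- **The loss is slight.** One point of power is small beside the uncertainty in a difference and SD borrowed from a study of another product, a mix of chicory inulin and FOS. This is true, and no design decision turns on the correction.
- **The shortfall at recruitment depends partly on rounding.** It is 3 per arm with the plan's 7.9 and 2 per arm with 7.85, so 69 and 207 should not be presented as the only correct figures. This also stands. It does not remove the mismatch, because 52.8 is below both 54.5 and 54.14.
- **The multiplication by 1.2 is inferred, not printed.** Correct, although the match is exact. The contradiction in step 3 does not depend on how 66 was obtained.
- **Children who drop out may still contribute.** The Statistical methods section plans multiple imputation or other suitable methods and a repeated-measures analysis, and stool consistency is recorded in weeks 1, 3, 6, 9 and 13. A child who leaves late may therefore supply data, and 79% is a completers-only figure. That is a fair caveat on the power figure. It does not repair the paragraph, which chose to budget for drop-out through sample size and misses its own target. Nor does imputation generally restore the information lost with a child who leaves.

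**Conclusion.** The point holds, and its size is small. Under the plan's own inputs, 66 per arm with 20% drop-out does not deliver the 54.5 per arm stated to be necessary. The gap is 1.7 completers per arm, equivalent to 2 or 3 children per arm at recruitment (6 to 9 in total). Power at that drop-out rate is about 79% instead of 80%.

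This rests on three readings: the drop-out rate is the fraction of recruited children lost, the test is two-sided at 0.05, and only completers count towards power. The first is the ordinary meaning and is not contradicted elsewhere; the second is implied by the printed constant; the third affects the exact power but not the mismatch between 52.8 and 54.5. It is an error in a stated justification, and it is no ground for calling the trial seriously underpowered.

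**What to change.** Keep 198 and correct the last sentence of the Sample size section. Either of these would be accurate:

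- *Recruiting 66 children per arm (198 in total) leaves the required 54.5 per arm provided drop-out does not exceed about 17%.*
- *Recruiting 66 children per arm (198 in total) leaves about 52.8 per arm at 20% drop-out, which gives about 79% power by the normal approximation.*

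The cost is one sentence and a slightly less favourable allowance or power figure. Enrolment, randomisation and analysis are unchanged.

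If the sponsor prefers to keep both 20% drop-out and 80% power, the target becomes 204 (unrounded quantiles) or 207 (the plan's 7.9), that is 6 to 9 more children. In that case, note that 204 = 34 × 6 can be filled with complete randomisation blocks of 6 and 12, whereas 207 is not a multiple of 6. For about one point of power, restating the figure is the proportionate choice, particularly as the Trial status section already reports delayed recruitment.

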### Assignment of interventions: allocation and blinding

Randomisation is done by a computerised random-number generator in the Electronic Data Capture system Castor EDC via a variable block randomisation of block sizes of 6 and 12, not stratified per centre, to one of the three intervention arms [35]. For the study product, two codes per treatment arm, each consisting of two letters and one number were made and printed on the bottom of the cans. The list linking these codes to GOS, FOS or the placebo is only known by two people who are not involved in this study; one at Wageningen University & Research and one at FrieslandCampina. Therefore, the study can be conducted fully blinded for all parties involved. In case of an emergency, the study treatment can be unblinded after consultation with the principal investigator at Wageningen University & Research.

## Data collection and management

### Plans for assessment and collection of outcomes

Data are collected via several means: a diary, weekly report, questionnaires and measurements and clinical symptom reporting during visits. Moreover, parents are asked to collect faecal samples.

#### Diary

The diary is sent daily in the morning via Castor EDC and contains questions on stool frequency and consistency for each defecation, reported for weeks 1, 3, 6, 9 and 13. Moreover, it contains a question on the use of escape medication and on the amount of study product that was consumed for that day. Lastly, in the diary, there is also room for reporting other, not urgent, problems such as mild GI symptoms.

#### Weekly report

The weekly report contains questions on the consumption of the study product (recall) and has room for other, non-urgent, issues such as mild GI symptoms.

#### Questionnaires

Three questionnaires are used in this study. The first one is a general questionnaire, which is only filled out once at the start of the study. This questionnaire includes questions on e.g. duration of breastfeeding and previous antibiotic treatment. Two other questionnaires are a quality of life questionnaire, filled out in weeks 1, 9 and 13. Lastly, to correct for changes in dietary habits, a food frequency questionnaire is filled out in weeks 1, 9 and 13.

#### Clinical symptoms

The Rome IV criteria are confirmed at the inclusion visit and are re-assessed at the end of the intervention period and during the close-out visit.

#### Faecal samples

Parents are asked to collect one faecal sample from weeks 1, 5, 9 and 13 from their child, and store it in a freezer until the close-out visit. Parents are instructed how to collect the sample and are provided with faecal sample tubes with an attached scoop and bags to safely store the sample in their freezer. These tubes are labelled with participant number, duration that the sample was outside of the freezer, date and stool consistency according to the mBSFS. During the close-out visit, faecal samples will be collected and transported on dry ice until they are stored in a -80°C freezer at Wageningen University & Research.

#### Other measurements

To ensure normal growth, anthropometrics (weight, height and head circumference) are measured during the inclusion and close-out visits by the researchers. Besides the reported consumption of the study product in the diaries, tins are weighed before and after the trial for each participant as an additional measure of compliance.

#### Data management and confidentiality

Collected data will be treated confidentially by the study staff associated with the project and according to Regulation (EU) 2016/679 of the European Parliament and of the Council of 27 April 2016 on the protection of natural persons with regard to the processing of personal data and on the free movement of such data, and repealing Directive 95/46/EC (General Data Protection Regulation, in Dutch the Netherlands ‘algemene veroderning gevevensbescherming’ (AVG)) guidelines. Consequently, codes are not based on personal data and are automatically provided by the online system used, i.e. Castor EDC. Data will be reported in electronic case reports (eCRF) and names of the research subjects will be coded, and this code will be used for study products, diaries and questionnaires. The codes list with both the codes and the names of the study participants and other source data will only be accessible to the coordinating investigator and principal investigators, Medical Ethical Committee (METC) and Health Care Inspectorate by a password-protected file in a secured online drive. Interim analyses are not planned.

### Statistical methods

#### Statistical analysis for primary, secondary and tertiary outcomes

Data will be presented as mean ± standard deviation (SD) if normally distributed, or median (interquartile range) when skewed. To test associations between continuous parameters, multiple linear regression will be used. For categorical or dichotomous outcomes, generalised estimation equations or mixed models for repeated measures will be used. Data will be tested for confounding or effect mediators, and confounding factors will be added to the regression. In case of missing data, they will be imputed by multiple imputation or other appropriate methods. All data will be assessed using the statistical program R (The R Foundation for Statistical Computing, Vienna, Austria). A *p*-value of < 0.05 will be considered statistically significant. In order to prevent p-hacking, a false discovery rate correction will be applied for microbiota analyses, of which a *q*-value of < 0.1 is regarded statistically significant. Either GOS or chicory FOS versus the placebo will be analysed for all parameters.

A variety of in-house R-scripts and the Phyloseq package will be used for microbiota composition analyses. To assess variation in microbiota composition, 16S rRNA gene sequence data will be tested for differences between groups in α-diversity (phylogenetic diversity; the number of observed species and inverted Simpson’s for evenness and richness) and β-diversity (Bray–Curtis dissimilarity distances, weighted and unweighted unifrac distances; methods for constrained and unconstrained ordinations; significance of variations by e.g. adonis test). Principal response curves will be used to check the development of the gut microbiota over time. Moreover, an area under the curve assessment for microbiota will be done. For 16S rRNA gene sequence data, a qPCR-based abundance of specific taxa selected based on sequence data and SCFA’s (multiple) linear regression will be used to test the predictive power of the model.

Changes in stool pH, results of the TAPQOL and changes in stool characteristics will be tested by a repeated measure analysis. Differences between timepoints will be assessed using mixed models.

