Importantly, this is one of the few studies that also gives insight into the gut microbiota of functionally constipated children, besides the impact of prebiotic oligosaccharides on the microbiota. Recently the gut microbiota has been implicated increasingly in not only bowel habit effects but also systemically on metabolism, immunity and the gut-brain axis [38]. Depending on bowel habit outcome effects, it may give some unique insights into the role of the gut microbiota. Moreover, this study will help to further characterise microbial signatures that may be linked to clinical subgroups of children with FC [39]. This might enable us to analyse in detail, which gut microbiota profiles and/or specific microbial populations may be predictive of a positive response, or lack thereof, to treatment with FOS or GOS. Besides the direct symptomatic and microbiological effects, the tertiary outcomes in this study of health-related quality of life and the need for escape medication will provide valuable insight into the perceived wellbeing of children with FC.

Our study has several strengths. First, this study covers many of the clinical outcomes, which are of major interest to clinicians and parents and takes into account most outcomes as suggested by the core outcome set for clinical trials in children with constipation [40]. These include stool consistency and frequency, painful defecation, quality of life of patients and parents, side effects of treatment, and if age-appropriate faecal incontinence [40]. Another strength is that this study also investigates the composition of the gut microbiota, as well as its activity in terms of pH and SCFAs, and the potential role of the gut microbiota in the treatment of FC in children. Moreover, this study also takes into account dietary intake, to also be able to correct for general fibre and fluid intake.

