A potential challenge for this study, arising from the nature of the condition, is that many functionally constipated children exert stool-withholding behaviour around the age of toilet training [41]. This behaviour is difficult to address, since the vicious cycle of withholding behaviour, and consequently, the passage of hard and large stools has to be broken. In clinical practice, this cycle is attempted to be broken by giving a higher dose of laxatives, of which the dose is adjusted to the child’s need, due to which a child cannot exert this withholding behaviour. However, this study uses the same dose for all children to first investigate whether prebiotic oligosaccharides may help in the treatment of FC. Within this study, we can differentiate between the children with and without stool-withholding behaviour. However, In case prebiotic oligosaccharides are found to be effective in functionally constipated children, a dose–response study would be a valuable addition to more effectively target those who exert intense stool-withholding behaviour.

A possible limitation of this study is that during this trial current medication use has to be stopped and this might result in (unsatisfactory) changes in bowel habits. Moreover, stopping current treatment and the fact that there is a chance of being in the placebo group might be a disincentive for parents to include their child in this trial. Secondly, the use of rescue medication, despite being selected to have the least influence on gut microbiota composition, will influence bowel habits. However, from the diaries, we can evaluate whether the bowel movement was spontaneous or after the use of rescue medication, although it will be impossible to rule out any potential longer-term influence of the rescue medication on bowel habits. Thirdly, the group of children with FC is very diverse. Therefore it may be a challenge to correct for potential (confounding) factors such as the differences in stool consistency which is known to influence gut microbiota composition, parental child-rearing attitudes and stress factors [42].

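### Covariates are chosen by testing the trial data for confounding, with no limit to pre-product measures, so diet recorded after product intake may enter the between-arm models

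*Protocol article*

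**What the plan says.** All references are to the Protocol article.

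- **Statistical analysis for primary, secondary and tertiary outcomes:** "Data will be tested for confounding or effect mediators, and confounding factors will be added to the regression". No candidate variables, test or threshold are given, and nothing restricts the choice to baseline measures. The same section assigns multiple linear regression to associations between continuous parameters, and a repeated-measures analysis to changes in stool characteristics.
- **Questionnaires:** the stated purpose of the dietary instrument is "to correct for changes in dietary habits, a food frequency questionnaire is filled out in weeks 1, 9 and 13".
- **Discussion and conclusion:** recording diet is presented as a strength, "to also be able to correct for general fibre and fluid intake". Among the limitations, the authors say it may be hard to "correct for potential (confounding) factors such as the differences in stool consistency which is known to influence gut microbiota composition".
- **Tertiary objectives:** one listed outcome is "Dietary intake, as measured by a food frequency questionnaire".
- **Primary objective:** the target is the mean difference in stool consistency for each prebiotic against placebo, at each diary week and from baseline to week 9.
- **Participant timeline:** randomisation comes before the one-week run-in, and product intake follows the run-in. The week 1 FFQ is therefore after randomisation but before product. The week 9 and week 13 FFQs are after both.

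**The concern.** Under randomisation, any difference between arms in a pre-treatment variable is due to chance. A test for confounding then says little about whether a covariate should be in the model. That depends on how well the covariate predicts the outcome, and it can be decided in advance.

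The more serious issue is timing. A rule that looks for confounders in the trial data, without a cut-off in time, can pick up variables that lie downstream of treatment. Data alone do not distinguish a confounder from a mediator or from a consequence of the outcome. The one adjustment purpose the protocol spells out, correcting for change in diet, needs exactly such variables. Parents may alter fibre or fluid in response to how the child's stools are going, or the product may itself alter what the child eats or drinks. In either case a model that conditions on week 9 or week 13 diet no longer estimates the total effect named in the Primary objective. Listing the same variable as an outcome makes this more awkward, because the trial itself allows that diet may differ by arm.

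**Working it through.** **1. The plan's own figure, for scale.** The Sample size section gives a difference of 0.35, an SD of 0.65, two-sided α of 0.05 (implied by the constant 7.9) and 80% power:

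n = 2 × 7.9 × (0.65/0.35)² = 54.49 per arm.

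This reproduces the stated 54.5. At 55 per arm, power for 0.35 is 80.6%. Nothing in the concern turns on this figure; it sets the scale for the illustration.

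**2. Diet affected by product and affecting stools.** The documents give no figure for either link, so both are assumptions. Let product shift the post-product covariate by *a* SD, and let the covariate shift consistency by *b* outcome SDs per SD. The part of the effect passing through the covariate is 0.65 × *a* × *b*, and adjustment removes it:

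adjusted estimate = 0.35 − 0.65 × *a* × *b*

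| a | b | Both links positive | One link negative |
|---|---|---|---|
| 0.3 | 0.3 | 0.35 − 0.0585 = 0.29 | 0.35 + 0.0585 = 0.41 |
| 0.5 | 0.5 | 0.35 − 0.1625 = 0.19 | 0.35 + 0.1625 = 0.51 |
| 0 | any | 0.35 | 0.35 |

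The last column is not far-fetched. If parents of children who do not improve raise fibre, and fibre softens stools, the active arm has the lower covariate. The indirect path is then negative and adjustment inflates the estimate.

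**3. Diet only reacting to stools.** Suppose diet responds to stool outcome with within-arm correlation *r* and does not feed back. The within-arm slope of outcome on diet then absorbs a share *r*² of the arm difference:

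adjusted estimate = 0.35 × (1 − *r*²)

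- *r* = 0.3: 0.35 × 0.91 = 0.32
- *r* = 0.5: 0.35 × 0.75 = 0.26

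Here the estimate shrinks whatever the sign of *r*. Taken with step 2, the direction cannot be known in advance.

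**4. Simulation check of step 2.** Least squares was used with 55 per arm, total effect 0.35 and SD 0.65. The covariate effect was 0.2 points per SD (0.2/0.65 = 0.31 outcome SD), with both links positive.

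| Shift in covariate (SD) | Adjusted estimate | Power, unadjusted | Power, adjusted |
|---|---|---|---|
| 0 | 0.349 | 79% | 84% |
| 0.2 | 0.31 | 80% | 74% |
| 0.3 | 0.29 | 80% | 67% |
| 0.5 | 0.25 | 81% | 54% |

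The first row also shows the benefit of a predictive covariate that treatment cannot affect: no bias and better power.

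**5. Does selection alone inflate the type I error?** Simulated under no effect, with six candidate baseline covariates:

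- fixed model with all six: 5.0%
- fixed 10% change-in-estimate rule: 3% to 5%
- smallest p among eight models (unadjusted, each covariate alone, all six): 10% to 13%

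A fixed selection rule does no harm to the type I error. Only an open choice steered by the p-value does, and the protocol does not describe that.

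**The case against.** The other side has several good points.

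- **Scope.** The sentence follows the one on linear regression for associations and refers to adding factors to that regression. Stool characteristics are assigned to a repeated-measures analysis. The trial also has genuine association analyses, such as stool characteristics against microbiota, where confounder adjustment is proper. This stands as an ambiguity, but the subsection heading covers every outcome and nothing exempts the arm comparisons.
- **Mediators.** A reader might infer that mediators will be adjusted away. The text does not say so: it tests for both kinds of variable but adds only confounding factors. What remains is that a test on the data cannot reliably sort one from the other.
- **Diet.** A reader might infer a commitment to put week 9 or 13 diet into the primary model. Neither the Questionnaires section nor the Discussion names that model, and the Discussion gives no time point. Week 1 diet would be harmless. The wording about change in diet does, however, require later values.
- **Stool consistency.** A reader might infer that the microbiota contrast will be adjusted for post-treatment stool consistency, the primary outcome variable. The passage is a remark on how varied these children are and how hard correction may be. It commits to nothing.
- **Likely size.** Blinding, identical tins and the bar on fibre supplements make a large diet difference between arms less likely. No document figure supports a shift of 0.3-0.5 SD.
- **Unseen SAP.** A covariate list may sit there. The point here is the rule that the protocol states, not the absence of a list.

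**Conclusion.** The point holds as a should-fix. The protocol states a data-driven rule for choosing covariates, under a heading that covers all outcomes and without limiting it to pre-product measures. It also describes a dietary correction that needs post-product values of a variable listed as an outcome. Followed in a between-arm model, this can move the estimate off the total effect of GOS or FOS.

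The size is unknown. On the assumed 0.3-0.5 inputs a true 0.35 becomes 0.19-0.29, or 0.41-0.51 with one link reversed. The bias is zero if diet responds neither to product nor to stool outcome. The documents do not support a claim that the primary effect will be attenuated, that a given amount of power will be lost, or that the type I error is inflated. The first two rest on assumed links of a particular sign and strength; the third needs a p-value-driven choice that the protocol does not describe.

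**What to change.** For all comparisons of GOS or FOS with placebo (primary, secondary, tertiary and microbiota), replace the confounder-testing sentence with a short covariate list fixed before unblinding and measured before product intake: the week 1 value of the outcome, age and, if wanted, week 1 fibre intake. Week 1 measurements qualify because they precede product intake, although they follow randomisation.

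State that week 9 and week 13 diet and post-baseline stool consistency enter only analyses labelled exploratory or mediation. Reword the Questionnaires section to match, so that the later FFQs serve the tertiary outcome and those exploratory analyses. Confounder adjustment can stay for the non-randomised associations, such as stool characteristics against microbiota, and the text should say that it applies there.

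The cost is wording in the protocol and SAP. No data collection changes, the diet-adjusted results can still be reported under their label, and a predictive pre-product covariate can improve precision.

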### Outcomes

#### Primary objective

The main study parameter is the change in stool consistency, measured by the validated Dutch-modified Bristol Stool Form Scale (mBSFS) [33]. This will be the mean difference in stool consistency of GOS versus placebo and FOS versus placebo at all time points (week 1, 3, 6, 9 and 13) and from baseline to week 9.

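### The change-in-mBSFS analysis lists the pre-product week 1 as an outcome week and names no baseline term; as written this points to raw change-score precision, which conditioning on week 1 would improve at no cost

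*Protocol article*

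**What the plan says.** Under Primary objective the article states: "The main study parameter is the change in stool consistency". Each active arm is compared with placebo on the mean difference "at all time points (week 1, 3, 6, 9 and 13) and from baseline to week 9".

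Week 1 precedes treatment. Participant timeline reads: "After randomisation, patients will enter a 1-week run-in period, after which they will either receive GOS, FOS or a placebo for 8 weeks". The week-1 score is also collected: under Diary, the daily form "contains questions on stool frequency and consistency for each defecation, reported for weeks 1, 3, 6, 9 and 13".

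The section on statistical analysis for primary, secondary and tertiary outcomes has three sentences that could bear on this outcome:

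- For change in the stool outcomes, it says: "Changes in stool pH, results of the TAPQOL and changes in stool characteristics will be tested by a repeated measure analysis".
- For continuous variables in general, it says: "To test associations between continuous parameters, multiple linear regression will be used".
- For comparisons between weeks, it says: "Differences between timepoints will be assessed using mixed models".

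None of them says how the week-1 stool score enters the model. The only rule on covariates is that the data will be checked for confounders and mediators, and that confounders found in this way go into the regression.

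**The concern.** The article treats week 1 in two ways: as the baseline from which change is measured, and as one of the weeks at which arms are compared. No product has been given by then, so the true arm difference is zero by design. A model that still estimates an arm difference at week 1 uses the baseline only by subtracting it, and the baseline's sampling noise goes into the treatment estimate in full. A model that conditions on week 1, or holds its mean equal across arms, removes that part of the noise.

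Two things are at stake. One is precision on the primary contrast, in a trial sized at 80% power with no allowance for baseline correlation. The other is prespecification: if baseline mBSFS enters only when a confounding check selects it, the primary model depends on the trial's own data.

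**Working it through.** **Inputs.** From Sample size: difference D = 0.35, SD = 0.65, 66 per arm, 20% drop-out. The article does not say whether 0.65 is the SD of change or of a score in a single week. The baseline-to-week-9 correlation r is not given; I assume 0.3, 0.5 and 0.7.

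**The plan's own figure.** 2 × 7.9 × (0.65/0.35)² = 54.49, which reproduces the stated 54.5 per group. The formula has no term for r. Completers per arm: 66 × 0.8 = 52.8, about 53. Power = Φ(D/SD × √(53/2) − 1.96) = Φ(2.772 − 1.96) = 79%.

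**Variances.** With the same variance σ² at baseline and week 9:

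- change score: 2σ²(1 − r)
- adjusted for baseline: σ²(1 − r²)
- adjusted divided by change: (1 + r)/2 = 0.65, 0.75, 0.85, which is a cut of 35%, 25%, 15%.

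The direction does not need equal variances. With baseline SD σ₀ and week-9 SD σ₉, the change-score variance minus the adjusted variance is (σ₀ − rσ₉)², which is never negative. The size of the cut does depend on that assumption.

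**Does a repeated-measures model avoid the loss?** I take the generalised least-squares variance of the week-9 effect for five weeks, compound symmetry, SD 0.65 and 53 per arm:

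| r | week-1 means free, change contrast | week-1 means constrained equal | ratio |
|---|---|---|---|
| 0.3 | 0.02232 | 0.01451 | 0.65 |
| 0.5 | 0.01594 | 0.01196 | 0.75 |
| 0.7 | 0.00957 | 0.00813 | 0.85 |

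The free-means model gives exactly the change-score variance, for example 2 × 0.4225 × 2 × 0.7/53 = 0.02232 at r = 0.3. The constrained model gives the adjusted variance. How week 1 is handled decides the matter.

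**Power if 0.65 is the SD of change.** The adjusted SD is 0.65 × √((1 + r)/2).

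| r | adjusted SD | power, change score | power, adjusted | n per arm for 80%, adjusted (change score: 55) |
|---|---|---|---|---|
| 0.3 | 0.524 | 79% | 93% | 36 |
| 0.5 | 0.563 | 79% | 89% | 41 |
| 0.7 | 0.599 | 79% | 85% | 47 |

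**Power if 0.65 is the SD of a single-week score.** The change SD is 0.65 × √(2(1 − r)); the adjusted SD is 0.65 × √(1 − r²).

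| r | change SD | power, change score | adjusted SD | power, adjusted |
|---|---|---|---|---|
| 0.3 | 0.769 | 65% | 0.620 | 83% |
| 0.5 | 0.650 | 79% | 0.563 | 89% |
| 0.7 | 0.503 | 95% | 0.464 | 97% |

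In this second case an unadjusted comparison of week-9 scores has 79% power at every r, so adjustment improves on that too.

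**Chance imbalance.** If 0.65 is the single-week SD, the standard error of a baseline difference between two arms is 0.65 × √(2/53) = 0.126, or 36% of the 0.35 target. A change score passes a fraction (1 − r) of any such difference into the estimate: 0.088, 0.063 and 0.038 at r = 0.3, 0.5 and 0.7 for a one-standard-error imbalance.

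**The case against.** The strongest reply is that non-adjustment is being read from silence. No sentence excludes a baseline term, the regression is allowed covariates, and a condensed article commonly leaves such detail to the full protocol or SAP. This stands against any claim that the plan rules out baseline adjustment. It does not dispose of the point, which rests on something the article does state: week 1 is listed as a between-arm comparison week.

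A second reply is that listing week 1 among the outcomes also suits a model with a constrained common baseline. That does not fit the wording. An arm difference at week 1 cannot be estimated if it has been set to zero.

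A reader might also infer that the article names two contradictory methods. It does not. A mixed model is one form of repeated-measures analysis, and the linear-regression sentence concerns associations between continuous parameters. The fair remark is only that no single primary model is spelt out.

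Nor is week-1 noise shown to be large in every child because stools are few. Two or fewer defecations a week is one of several Rome IV items in Table 1, of which two are needed, so a sparse baseline is plausible for some children and not established for all.

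Lastly, change scores are unbiased under randomisation, and the primary objective also includes plain between-arm differences at later weeks, which carry no baseline noise. Both are true. The matter is efficiency, not validity.

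**Conclusion.** The point holds as an improvement that should be made. As written, the primary objective and the analysis section together point to a model with free week-1 means, whose baseline-to-week-9 contrast has raw change-score variance, and the only route for a baseline covariate is data-driven. Conditioning on week 1 would cut that variance by 35% to 15% for r from 0.3 to 0.7 with equal variances. Power with about 53 completers per arm would rise from 79% to between 93% and 85% if 0.65 is the SD of change, or from 65%–95% to 83%–97% across the same r if it is a single-week SD.

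The direction of the gain is secure. Its size is not, because r, the type of SD and the equality of variances are all undocumented. At r = 0.7 with a single-week SD the gain in power is only about 3 percentage points.

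**What to change.** State one primary model: a linear mixed model for each child's weekly mean mBSFS at weeks 3, 6, 9 and 13, with arm, week, arm-by-week and the prespecified week-1 mean mBSFS (with its own coefficient for each week). Alternatively, keep week 1 as an outcome with its mean constrained equal across arms. The second form also retains children with no stool in week 1, whom the covariate form would drop unless their baseline is imputed.

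Drop the between-arm comparison at week 1 as an outcome. Read the baseline-to-week-9 effect from the adjusted week-9 contrasts, GOS versus placebo and FOS versus placebo. Include baseline mBSFS whatever the confounding check shows.

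The cost is wording in the protocol or SAP, settled before unblinding. The week-1 diary is already collected, so no visit, measurement or child is added.
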